## Abstract

**Introduction:**

Recent research from both human and animal studies confirms that cognitive training gains a considerable effect on multiple cognitive domains in older adults with mild cognitive impairment. Previous studies have yet paid scant attention to executive function training. Little is known about whether this specific benefit translates to maintaining long-term effectiveness and transfer effects are. This study is designed as an effort to address this issue.

**Objective:**

The program aimed to evaluate the effect of process-based multi-task cognitive training on executive function and further explore its long-term effects and transfer effects in older adults with MCI. Furthermore, we will explore the neural correlates latent the changed performances underlying the cognitive intervention.

**Methods:**

This program is a single-blinded, randomized, prospective clinical trial to test the effect of process-based multi-task cognitive training in older adults with MCI. Ninety participants with MCI will be recruited and randomly assigned to the cognitive training group (n=45) and the wait-list control group (n=45). The cognitive training group will receive 10 weeks of process-based multi-task cognitive training and health education twice a week, at 40~60 min per session. While the wait-list control group will only receive 10 weeks of health education during the research period. The effect is measured using the executive function, neuropsychological assessment performance and related brain activity assessed with electroencephalogram parameters (slowness and complexity of the EEG) at baseline, after 10 weeks of training, and a 3-month follow-up.

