The calculation of sample size is based on the change in executive function after 10-week, which is the primary outcome variable in this study. A meta-analysis found that significant benefits of cognitive training are superior to the wait-list and the effect size of executive function training used to calculate the sample size is 0.575 [0.093,1.056] (18, 19). Sample size estimation was conducted using statistical software G*power. In the analysis with an independent t-test using a power of 80% and a type 1 error of 5%, the calculated total sample for this study is 78. Considering a 15% dropout rate and maximum to ensure the credibility of the cognitive training, we will recruit 46 participants in each group. Thus, the total required sample size for this study is 92 participants.

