#### Study Procedure

Participants will be enrolled from the nearby community health service centre via open recruitment through paper flyers, online forums, and word-of-mouth. Participants who interested in this program will be invited for an in-person interview to complete a screening questionnaire in the community health service centre, including demographic characteristics, MMSE, MoCA, ADL, and Achromatopsia anomalous trichromatic test (AATT). A trained physician in community health service centre will invite the potential participants to undergo a physical examination and neurologic diagnosis of MCI. Participants who met the eligibility criteria will be assessed with a baseline assessment and then given the EEG evaluation in the 2 days preceding the start of the cognitive training.

After that, according to the random allocation sequence, participants will be randomly assigned to one of two groups with a targeted assignment ratio of 1:1. The random allocation sequence with a block size of four will be generated using a computer randomization list by an independent researcher assistant. The random allocation sequence is sealed in opaque envelopes by an assistant. The cognitive training group will receive cognitive intervention and health education, whereas the wait-list control group will only receive health education during the research period. During the 3 months follow up, the cognitive training group and wait-list control group will receive no interventions. Complete all outcome assessments, participants in the wait-list control group will be permitted to undergo the process-based multi-task cognitive training program. Although it was not initially the plan, the health education manual for mild cognitive impairment will be provided for participants who are not finishing the cognitive training or health education through various means, such as email, public platform, and short messaging service. All outcome measurements will be assessed at baseline, 10 weeks and 3 months follow up. Study assessments and timelines are illustrated in **Table 3**.

**Table 3 T3:** Summary of study assessments and timelines.

Time point	Measurement	Post-allocation					Mode of Administration
		Baseline	Training sessions	10 weeks assessments		Follow-up 3 months	
		T0		T1		T2	

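### The abstract plans to recruit 90 participants (45 per group) but the sample-size paragraph requires 92 (46 per group), and only 92 follows from the plan's own 78 evaluable and 15% dropout

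*Protocol article*

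**What the plan says.** The Methods paragraph of the abstract gives the number to be recruited and allocated: "Ninety participants with MCI will be recruited and randomly assigned to the cognitive training group (n=45) and the wait-list control group (n=45".

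The sample-size paragraph, which follows Table 1 under Study Design and Participants, gives a different number and shows where it comes from. From a standardised effect of 0.575, an independent t-test, 80% power and a 5% type 1 error, "the calculated total sample for this study is 78". The allowance for loss follows: "Considering a 15% dropout rate and maximum to ensure the credibility of the cognitive training, we will recruit 46 participants in each group". It concludes: "Thus, the total required sample size for this study is 92 participants".

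Both statements look forward and describe the same quantity. Neither is marked as approximate or superseded, and the article does not explain the difference.

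**The concern.** The number to recruit is a core design figure, and a plan should state it once. The two numbers cannot be reconciled by reading one as recruited and the other as evaluable, because the sample-size paragraph gives the evaluable number separately as 78. Nor does condensing a longer protocol into an article explain it, since both figures are printed in full in the same article and disagree.

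The abstract is the part most often read and cited, and it carries the figure that does not follow from the calculation. Anyone taking the planned number from the abstract would count an enrolment of 90 as complete. Anyone taking it from the sample-size paragraph would count it as two short.

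**Working it through.** **Inputs, all from the protocol article**
- Abstract, Methods: 90 recruited, 45 per group.
- Sample-size paragraph: 78 evaluable (39 per group), 15% dropout, 92 recruited (46 per group), effect size 0.575, independent t-test, power 80%, type 1 error 5%. Sidedness is not stated.

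**Step 1: reproduce the plan's 78.** For a two-sample t-test (noncentral t) with d = 0.575, power 0.80 and alpha 0.05:
- one-sided: 38.09 per group, rounded up to 39, total 78;
- two-sided: 48.46 per group, rounded up to 49, total 98.

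The stated 78 is therefore reproduced by a one-sided 5% test and not by a two-sided one.

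**Step 2: reproduce the plan's 92.** Recruited = evaluable / (1 − dropout).
- Total: 78 / 0.85 = 91.8, rounded up to 92.
- Per group: 39 / 0.85 = 45.9, rounded up to 46.

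The sample-size paragraph is correct on this step.

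**Step 3: test both targets against 78.** Evaluable = recruited × (1 − dropout).
- 92 × 0.85 = 78.2, which meets 78.
- 90 × 0.85 = 76.5 (38.25 per group), which is 78 − 76.5 = 1.5 short.
- To keep 78 out of 90, dropout could be at most 1 − 78/90 = 13.3%, against the 15% assumed.

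**Step 4: a possible origin of 90.** Multiplying by 1.15 instead of dividing by 0.85 gives 78 × 1.15 = 89.7, which rounds up to 90. That this is how the abstract's figure arose is an inference; the article does not say.

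**Step 5: size in terms of power** (d = 0.575, alpha 0.05)

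| Evaluable per group | One-sided | Two-sided |
|---|---|---|
| 38 | 0.799 | 0.696 |
| 38.25 (90 recruited, 15% lost) | 0.801 | 0.699 |
| 39 (the plan's 78) | 0.808 | 0.708 |

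Between 38.25 and 39 per group the difference is 0.808 − 0.801 = 0.007 one-sided and 0.708 − 0.699 = 0.009 two-sided, less than one percentage point either way.

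**The case against.** The strongest reply is that the operative figure is not really in doubt. The sample-size paragraph is the place for it, shows its derivation and calls 92 the required number, while the abstract is a summary with no derivation. The consequence is two recruits, and no analysis or conclusion changes. This stands as to size, and it supports correcting the abstract rather than the calculation. It does not remove the contradiction, because the abstract states its number, with group sizes, just as firmly.

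Three stronger readings are tempting, and the document does not support them.

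- *That 90 loses the stated 80% power while 92 keeps it.* Power falls below 0.80 only if 38.25 per group is rounded down to 38 (0.799); unrounded it is 0.801. The contrast also needs a one-sided test, which the article never states. On a two-sided test both targets give about 70%.
- *That 90 conflicts with the randomisation because it is not a multiple of the block size.* Study Procedure says: "The random allocation sequence with a block size of four will be generated using a computer randomization list by an independent researcher assistant". The 1:1 ratio is described there only as targeted. An unfinished last block is routine; with balanced blocks it can do no worse than 46:44, and it is not an error.
- *That enrolment would stop at 90.* Nothing in the article makes the count a stopping rule. The Trial Status section gives only a calendar end, the end of 2020.

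**Conclusion.** The point holds as a contradiction between two stated recruitment targets, one of which fails the plan's own arithmetic. Given 78 evaluable and 15% dropout, 92 is right, and 90 leaves 76.5, a shortfall of 1.5. This conclusion needs no assumption beyond those two stated inputs and is the same whichever way the test is sided.

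The practical effect is small, under one percentage point of power, so this is a correction to a stated design figure and not a finding that the trial is underpowered because of the abstract. Nor should 92 be read as having been shown adequate. It is the correct inflation of 78, but 78 itself is reproduced only by a one-sided 5% test. With the same inputs two-sided, the evaluable number would be 98, and 39 per group gives about 71% power. That is a separate question, which agreeing on 92 does not settle.

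**What to change.** In the Methods paragraph of the abstract, change the target to 92 participants, 46 in each group, so that it agrees with the sample-size paragraph.

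If the sponsor in fact fixed 90, leave the abstract and restate the sample-size paragraph instead: 90 recruited, about 76 evaluable after 15% dropout, the power that this gives, and whether the test is one-sided or two-sided. At 38 per group that power is about 0.80 one-sided or 0.70 two-sided.

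Either change costs wording only. The first asks for no participants beyond the 92 that the sample-size paragraph already requires.

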**Results:**

The study is currently ongoing. Recruitment began in March 2019 and will conclude at the end of 2020. Effects of the process-based multi-task cognitive training on executive function in older adults with MCI will be described in intention-to-treat analysis and protocol set principle. We will also explore the potential long-term effects and transfer effects.

**Discussion:**

If a process-based multi-task cognitive training program results in positive changes to executive function in older adults with MCI, this might provide a viable and potential approach to delay the cognitive decline.

**Clinical Trial Registration:** ChiCTR1900020585. Registered on January 09, 2019. http://www.chictr.org.cn/showproj.aspx?proj=34664.

## Highlights 

This paper describes the process-based multi-task cognitive training program study, an implementation study to improve the effect on executive function in community elderly with mild cognitive impairment in China. This is the first nurse-led cognitive training program conducted in the community of Zhejiang Province.Previous studies have yet paid scant attention to executive function training. The program adapts the maximum of the optimal training volume to explore whether adequate training could improve executive function.It provides an example of a more cost-effective and feasible cognitive training method and uses dynamic and hierarchical tasks to implement efficiency and suitable.

## Background

Mild cognitive impairment (MCI) represents an intermediate state between normal or healthy ageing and early-stage dementia (1). The annual progression rate from MCI to AD or other types of dementia is 10%~59.4% (2–4), while the proportion from healthy elderly to AD is only 1%~3% (5, 6). Practice guidelines and meta-analysis reported that 14.4%~55.6% of those with MCI revert to normal cognition (NC) (4, 5, 7). The reversion from MCI to NC maybe benefit from appropriate cognition management/intervention (8). Therefore, the stage of MCI provides a critical window of opportunity for the prevention and treatment of dementia.

Although memory impairment is a major manifestation of MCI, preclinical deficits in executive function are widely observed in older adults with MCI (9, 10). Seo pointed out that executive function has been shown to interact with memory function (10). More importantly, the executive function is a crucial predictive factor in dementia prognosis (11). Older adults with MCI with lower executive function demonstrated more often develop into AD after 1 year than those with higher executive function (12). Recently, a growing body of researches on cognitive training has focused on executive dysfunction and found that it could improve executive function performance (13–15). The improvements in executive function are potentially extremely relevant with daily living capacities of older adults (11, 16). Therefore, executive function is considered to be a crucial cognitive domain of the prevention and treatment of MCI.

Cognitive training as a means to counteract cognition decline with high practical operability and no side effects, and has demonstrated its benefits on cognitive function for the older adults with MCI (17–19). In 2017, a review commissioned by the American Academy of Neurology (AAN) recommended that cognitive training may be provided with a beneficial practice in improving measures of cognitive function in older adults with MCI (4). Meanwhile, older adults with MCI in early-stage benefit from neural reorganization, which were induced by cognitive training targeting at executive function (18, 20). Neuroimaging findings also have indicated that cognitive training focus on executive function for normal elderly has been associated with increased neurocognitive activation and cognitive control network connectivity (e.g., frontoparietal network, occipito-temporal regions) (21, 22). Therefore, executive function as a successful compensatory mechanism for cognition improvement could be significant (19, 20).

However, some systematic reviews and RCT studies have reported several limitations frequently occurred in the cognitive training, including an emphasis on single-modality training tasks (23), failure to adjust the cognitive training tasks and the level of difficulty on the training tasks throughout the process of cognitive training (24), and transfer effects of cognitive training to other untrained cognitive domain can be little known (15). Besides, studies of process-based executive function training revealed that more considerable training-related benefits in older adults than in younger adults (25, 26). However, previous process-based cognitive training studies in older adults with MCI did not put sufficient training on the executive function (18, 19).

It remains not entirely clear how cognitive training related mechanisms affect executive function in older adults with MCI. Electroencephalography analysis provides a good indication of the neurological integrity of the central nervous system (27), which would increase our insight into the mechanisms of any potential effects of cognitive training targeting at executive function (28).

Given that the limitations of cognitive training for older adults with MCI reported by previous researches, we developed a process-based multi-tasks cognitive training program based on the process model (29, 30),****which was targeted to improve the executive function of older adults with MCI. The primary aim of this study is to evaluate whether the process-based multi-task cognitive training program would provide better results on executive function in older adults with MCI. The secondary aim is to explore whether potential training effects will be able to generalize to other untrained cognitive domains (transfer effects), and those effects will be maintained effectiveness over 3 months of follow-up (maintaining effect). The tertiary aim is to explore the changed performances of brain neural activity underlying the process-based cognitive training targeting at executive function.

## Materials and Methods

### Study Design and Participants

This study will be a randomized controlled trial (Clinical Trials.gov number: ChiCTR1900020585) with 10 weeks of cognitive training and 3 months of follow-up. The participants will be recruited via advertisements from community healthcare service centre in Huzhou, Zhejiang Province, China. The community healthcare service centre provides comprehensive services, from prevention, screening, and early detection to long-term care that engages communities. The study procedure is shown in **Figure 1**. This program will consist of two arms: the cognitive training group (process-based multi-task cognitive training and health education classes) and the wait-list control group (health education classes). The wait-list group will access to attend the same program after the cognitive training group had completed a 3-month follow-up.

**Figure 1 f1:**
[figure not shown]
Overview of study procedure..

Participants are community-dwelling older adults, both men and women, aged 60 years or older who meet Petersen criteria will be included (31). Participants who meet the following criteria will be allowed to withdraw from this program, having severe medical events that occurred during the training or follow-up period, and should not continue to receive this program, reluctant themselves in training at any time, and a major protocol violation. Detailed inclusion and exclusion criteria are listed in **Table 1**. This study will be carried out following the recommendations of SPIRIT Guidelines with written informed consent from all participants who meet inclusion criteria or their surrogate family members. Ethical approval was approved by the Medical Ethics Committee of the Third People’s Huzhou Hospital of Zhejiang Province (number 2018-030).

**Table 1 T1:** Inclusion and exclusion criteria.

Inclusion criteria	Exclusion criteria
Fulfils the diagnostic criteria of MCI proposed by Petersen (31) Subjective or informant-reported of memory or cognitive decline/complaints Objective memory impairment (or other cognitive functions) inconsistent with age and educational background evaluated by age-adjusted scores at least 1.5 SDs below the mean on the Logical Memory subtest of Chinese version of the Wechsler Memory Scale-Revised (WMS-R) Preserved global cognitive function (MMSE ≥ 24; MoCA <26 when education level >12 years or MoCA <25 when education level≤12 years) Intact activities of daily living Do not meet dementia criteria. Aged 60 years or older Have at least primary school education (>5 years) No significant visual and hearing impairment and color blindness Willingness to participate in entirety of study Capacity to provide written informed consent	History of presence of a neurocognitive disorders (e.g. epilepsy, Parkinson’s disease, head trauma, stroke, mental retardation) and serious medical conditions that can cause brain dysfunction. Take cognitive enhancers, antidepressants in the last month History of presence of severe psychiatric disorders. (e.g., severe depression, active suicidal ideation, anxiety, schizophrenia and alcoholism and drug abuse); Participants in another training related to cognitive function or any investigational drug study at the same time

The calculation of sample size is based on the change in executive function after 10-week, which is the primary outcome variable in this study. A meta-analysis found that significant benefits of cognitive training are superior to the wait-list and the effect size of executive function training used to calculate the sample size is 0.575 [0.093,1.056] (18, 19). Sample size estimation was conducted using statistical software G*power. In the analysis with an independent t-test using a power of 80% and a type 1 error of 5%, the calculated total sample for this study is 78. Considering a 15% dropout rate and maximum to ensure the credibility of the cognitive training, we will recruit 46 participants in each group. Thus, the total required sample size for this study is 92 participants.

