#### Statistical Considerations

The primary and secondary outcome measures were analyzed using data from the intention-to-treat. Moreover, the protocol set principle was defined as those participants or the participants who completed at least 80% adherence to the program initially formulated and assessments all the required will be included. We will compare the characteristics of the completed participants versus dropout ones. Sensitivity analyses of completed participants will be further performed to explore the potential for dropout participants, and the results will be categorized as bias. Listwise deletion will be adopted to estimate treatment effects and sensitivity of the cluster dropout if missing values satisfy the criteria of the losing data entirely at random; otherwise, multiple imputation data strategies will be adopted.

Data processing and statistical analysis will be conducted using SPSS 21.0 and MatLab (The Mathworks Inc. 2016). Descriptive statistics will be reported as frequencies for categorical variables and means ± standard deviations for continuous variables. The adoption mainly the method of exploratory analysis to examine the distribution state of data. The proportionality of baseline data for both groups is compared by the non-parameters Wilcoxon test, chi-square test, and t-test. Regarding the primary outcome, a repeated ANOVA test will be used to evaluate the differences of changes and long-term effect in outcome measurement index performance in the cognitive training group and the wait-list control group, within-group over time, and interaction effects. The simple effect analysis will be added when there is an interaction between intervention factors and time factors. Secondary outcomes will be analyzed using similar statistical methods. The mediating effect model was used to test the transfer effect of cognitive training on untrained cognitive domains, with cognitive training as the mediator. A significant statistical will be considered as P < 0.05 for all comparisons. The effect size (r) was calculated using Cohen’s d to estimate the between-group effect sizes.

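### The total of 78 for 80% power follows only from a one-sided t-test that the protocol never declares; taken two-sided, the same t-test has about 71% power at 78 evaluable and needs 98 for 80%

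*Protocol article*

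**What the plan says.** The sample-size paragraph (Materials and Methods, Study Design and Participants) bases the calculation on the change in executive function at 10 weeks, the primary outcome. It takes its effect from meta-analysis: "the effect size of executive function training used to calculate the sample size is 0.575 [0.093,1.056" (the bracket is the reported interval). On software it says: "Sample size estimation was conducted using statistical software G*power". The result is given as "using a power of 80% and a type 1 error of 5%, the calculated total sample for this study is 78". Sidedness is not mentioned. Allowing for 15% dropout, "we will recruit 46 participants in each group", 92 in all. The Methods part of the abstract gives a different number: participants will be "randomly assigned to the cognitive training group (n=45) and the wait-list control group (n=45"), 90 in all.

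Statistical Considerations analyses the primary outcome by repeated-measures ANOVA, with group, time and interaction effects. The criterion is: "A significant statistical will be considered as P < 0.05 for all comparisons". No one-sided test is declared there or elsewhere in the article.

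**The concern.** A reader who meets a t-test, a 5% type 1 error and a P < 0.05 criterion, with no mention of direction, will assume a two-sided test. On that reading, an effect of 0.575 needs clearly more than 78 participants for 80% power. The calculation and the analysis then use different error rates: one appears to put the whole 5% in one tail, while the other rejects in either direction. What is at stake is whether the stated 80% can be relied on when the primary result is interpreted. The two randomised totals add a smaller problem, because it is unclear which one the trial is committed to.

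**Working it through.** **Inputs.** From the sample-size paragraph: independent t-test, d = 0.575 (read as a standardised mean difference), power 80%, type 1 error 5%, dropout 15%, G*Power (hence the noncentral t). From Study Procedure: 1:1 allocation. Sidedness is not given, so both versions were tried.

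**Formula.** With n per arm, the noncentrality is λ = d·√(n/2) on 2n − 2 degrees of freedom. One-sided power is P(T > t at 0.95). Two-sided power is P(|T| > t at 0.975).

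**Step 1: reproduce the plan's figure, one-sided.** Solving for 80% gives n = 38.09, so 39 per arm, total 78. At n = 39, λ = 0.575 × √19.5 = 2.54 and the critical value is 1.665 on 76 df; power is 80.8%. Dropout: 78 / 0.85 = 91.8, so 92. Both stated figures match exactly.

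**Step 2: the same inputs, two-sided.** n = 48.46, so 49 per arm, total 98. Dropout: 98 / 0.85 = 115.3, so 116. The normal approximation gives 48 per arm (96), so the gap is not a matter of method or rounding. At n = 39 the critical value rises to 1.992 and power falls to 70.8%.

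**Step 3: two-sided power at the numbers in the article.**

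| Evaluable per arm | Where it comes from | Two-sided power |
|---|---|---|
| 38 | 90 enrolled, 15% lost (76.5 left) | 69.6% |
| 39 | the planned 78 | 70.8% |
| 45 | 90 enrolled, none lost | 77.0% |
| 46 | 92 enrolled, none lost | 77.9% |

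From the planned 78 to a full 92, the chance of missing an effect of 0.575 is 100 − 70.8 = 29.2% down to 100 − 77.9 = 22.1%. With 39 per arm, the effect detectable at 80% two-sided is d = 0.643.

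**Step 4: the two totals.** 92 × 0.85 = 78.2, which covers the plan's 78. 90 × 0.85 = 76.5, which does not.

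**Step 5: what baseline adjustment could do.** Let r be the baseline to week-10 correlation, an assumption because the article gives none. At 39 per arm, 80% two-sided power needs an effective d of 0.643. The answer depends on the SD in which 0.575 is expressed.

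- *Week-10 SD units:* effective d = 0.575 / √(1 − r²). This reaches 0.643 when r is at least about 0.45. Power is 74.8% at r = 0.3, 80.2% at 0.45 and 88.0% at 0.6.
- *Change-score SD units:* effective d = 0.575 × √(2 / (1 + r)). This stays at or above 0.643 only while r is at most about 0.60. Power is 82.5% at r = 0.5, 80.0% at 0.6, 77.6% at 0.7 and 75.3% at 0.8.

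The direction of the condition reverses between the two readings.

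**The case against.** **Sidedness is unstated, not misstated.** The one-sided basis is inferred from the exact match. The aim is worded directionally in the Background, and the full protocol, which is not shown, may declare a one-sided test. If so, the arithmetic of 78 is correct. This stands as a caution against calling it a calculation error. It does not remove the conflict within the article: a directional aim does not define a rejection region, and the ANOVA F tests at P < 0.05 are non-directional.

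**The planned analysis is not the t-test.** A reader might infer that the trial, as it will be analysed, has 71% power. The document does not support that. The figure belongs to the sizing t-test. The power of the repeated-measures analysis depends on the correlation and on the scaling of 0.575. For example, if 0.575 is in week-10 SD units, a two-sided t-test on change at 39 per arm has 67% power at r = 0.45, 80% at r = 0.6 and 90% at r = 0.7. This objection stands in full, although the article claims no such gain and gives nothing from which to compute one.

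**71% assumes the whole dropout allowance is used.** This also stands. The 15% is a planning figure, and the analysis is by intention to treat, with multiple imputation if data are not missing completely at random. With all 92 evaluable the shortfall is about 2 points, hence the range of 22% to 29%. Even so, no enrolment figure in the article reaches 80% two-sided.

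**Other uncertainties are larger.** The interval for the effect, 0.093 to 1.056, moves power far more than sidedness does. That is true, but it does not make the stated figure follow from its stated inputs.

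**Conclusion.** The sample-size statement is wrong as written. At d = 0.575 and a 5% type 1 error, 78 gives 80% power only one-sided, and the article neither declares a one-sided test nor plans an analysis that matches one. Two-sided, the same t-test has about 71% power at 78 evaluable and about 78% at 92, and it needs 98 evaluable for 80%. This rests on reading 0.575 as a standardised mean difference and on inferring the one-sided basis from the exact reproduction of 78 and 92.

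Two stronger readings are not supported. The 71% is not the power of the planned ANOVA, which cannot be computed from the article. Nor can it be said that baseline adjustment restores 80% whenever the correlation is at least 0.45: the sample-size paragraph refers to change in executive function, and if 0.575 is in change-score SD units the requirement becomes a correlation of at most about 0.60.

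The 90 versus 92 discrepancy is a separate inconsistency that holds whatever the sidedness. Its effect on power is about one point (69.6% against 70.8%).

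**What to change.** **Wording changes, no extra participants.**

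1. State the sidedness of the sample-size test and make it agree with the test in Statistical Considerations.
2. Restate the power: for d = 0.575, 78 evaluable gives about 71% two-sided (80% only one-sided), with a detectable effect of 0.64 at 39 per arm.
3. Give one randomised total in the abstract and the methods. If it is 90, say that 15% dropout leaves 76.5, below the 78 the plan sets itself.

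The cost is a less favourable stated power.

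**Optional, and not a wording change.** Power could be recovered without more participants by making the primary test the baseline-adjusted difference at week 10. This replaces the primary analysis in a trial that the Trial Status section describes as already recruiting, so it would need a dated amendment. It should come with a statement of the SD in which 0.575 is expressed and an assumed correlation: at 39 per arm, 80% two-sided needs at least about 0.45 in week-10 SD units, or at most about 0.60 in change-score SD units.
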